## 10.6 SAEs

For this trial, AEs that meet one or more of the following criteria are classified as SAE: death, life-threatening events, in-patient hospitalization or prolongation of existing hospitalization, a persistent or severe disability or incapacity, congenital anomalies/birth defects, or any AEs that, based upon appropriate medical judgment, may jeopardize the subject and may require medical or surgical intervention to prevent one of the outcomes listed above. Pregnancy in patients or their spouses will be reported as SAEs to the sponsor or their representative.

Disease progression (including signs and symptoms of progression) under the trial will not be reported as an SAE, but death due to disease progression during the trial or safety reporting period will be reported as an SAE. Hospitalization due to signs and symptoms of disease progression will also not be reported as an SAE. During the trial or safety reporting period, events leading to death must be reported as SAE in dead subjects.

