#### **3.2.2 Handling of Participant Withdrawals**

Investigators should clearly collect the reason and time of withdrawal, conduct corresponding observation and evaluation of the withdrawn subjects, complete the evaluation content when withdrawing from the study as specified in the study plan, fill in the corresponding original records, and describe the reasons for withdrawal. Subjects who discontinue the study should continue to be

followed for AEs. If possible, these subjects should continue to follow up AEs until it recovers to the baseline level or the investigator believes that follow-up observation is unnecessary.

During the study period, all subjects who received the drug but did not complete the relevant study content of the protocol should have their last examination results transferred to the final result. Subjects who did not follow up as required and evidence of contact should be recorded in the corresponding original records and electronic data collections (EDCs; such as time and date of telephone contact, mailing receipt of registered mail, etc.) and properly preserved.

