**Post-treatment Follow-ups**

All subjects will be followed up every 8 weeks (including telephone follow-up) to collect data on other antitumor therapy and disease status. The treatment regimens, cycles, and outcomes of any other treatment must be recorded during the trial. Post-treatment follow-up will be conducted until

death. Reasons and the date of death will be recorded for overall survival analysis.

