## **10. Safety Analysis**

### **10.1 AEs**

AEs are defined as any untoward medical occurrence in a patient or clinical investigation subject administered a pharmaceutical product and which does not necessarily have to have a causal relationship with this treatment. Thus, AEs could be any unfavorable and unintended sign (including an abnormal laboratory finding), symptom, or disease temporarily associated with the use of a medical treatment or procedure regardless of whether it is considered related.

AEs also include the complications resulting from the protocol-defined interventions, such as complications caused by tissue biopsy or other invasive procedures; and the worsening of underlying disease (except for tumor progression) assessed by the investigator(s) during the reporting period of AEs.

Investigator(s) are required to record any AEs in subjects, including the events, AEs-related symptoms, time of occurrence, severity, duration, management, and outcomes.

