### **Disease progression**

If the observed progression is confirmed to be consistent with the expected pattern of primary tumor progression, it will not be considered an AE. The hospitalization due to this progression will also not be considered an SAE. If symptoms cannot be confirmed to be caused by tumor progression, or consistent with the expected pattern, the events will be considered an AE or an SAE.

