### **10.4 Follow-up of AEs**

Investigator(s) are required to follow up all AEs until any of the following occurs:

- AEs resolve to baseline;
- No further remission will be expected by the investigator(s);
- Death;
- Lost to follow-up;
- AEs that are not related to the study treatment confirmed by the investigator(s);
- Starting new antitumor treatment;
- End of clinical or safety data collection, or the database lock;
- No clinical or safety data are collected, or the database is eventually closed.

The outcomes of each AE (including the date of resolution and death) need to be recorded in the CRF/eCRF.

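### Section 10.6 makes death from progression an SAE with no end date, although the protocol says expected progression is not an AE, and the safety tables do not separate these deaths

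*Protocol*

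**What the plan says.** Section 10.1 counts as an AE the "worsening of underlying disease (except for tumor progression", as judged by the investigator). Section 10.3, under Disease progression, says that if progression is "consistent with the expected pattern of primary tumor progression, it will not be considered an AE". Section 10.3, under Death, has investigators report as SAEs the deaths that are due to an AE and, provisionally, deaths of unknown cause.

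Section 10.6 defines SAEs as those AEs that meet a seriousness criterion. It then states "Disease progression (including signs and symptoms of progression) under the trial will not be reported as an SAE". The fatal case is carved out as an exception in the same sentence: "but death due to disease progression during the trial or safety reporting period will be reported as an SAE". The section's last sentence adds: "During the trial or safety reporting period, events leading to death must be reported as SAE in dead subjects".

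Section 7, under Post-treatment Follow-ups, states "Post-treatment follow-up will be conducted until" death. No section available to us defines the safety reporting period. The nearest windows serve other purposes: 28 days after the last dose for concomitant medication (section 8) and 30 days for pregnancy (section 10.3).

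Section 3.6 makes the incidence of SAEs a secondary endpoint. Section 13.5.2 tabulates SAEs as serious TEAEs, with treatment-related SAEs and TEAEs leading to death as separate entries.

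On the length of AE follow-up, section 10.4 lists "Starting new antitumor treatment" among the points at which follow-up of any AE ends. Section 3.2.2 says of patients who discontinue that, if possible, "these subjects should continue to follow up AEs until it recovers to the baseline level" or until the investigator considers it unnecessary.

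**The concern.** An event that is not an AE cannot belong to a class defined as a subset of AEs. An investigator reading 10.1 and 10.3 would record a progression death only as a survival event. One reading 10.6 would send an SAE report, to which section 10.7 attaches a 24-hour deadline and supporting documents. Because the rule runs *during the trial* as well as in an undefined safety reporting period, sites can differ on when the duty ends.

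The statistical stake is that death from progression is part of the efficacy outcome. If it is counted as a safety event, the arm whose disease is controlled less well collects more SAEs for that reason alone, and all-cause SAE incidence becomes a mixture of toxicity and disease.

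The two rules on AE follow-up raise a smaller, separate problem. For a patient who discontinues with an unresolved treatment-related SAE or irAE and starts another antitumour treatment, 10.4 ends follow-up while 3.2.2 asks for it to continue.

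**Working it through.** **1. How many deaths the open-ended rule would reach.** Inputs from section 4.1: control median OS 10 months, HRs 0.70 (arm 1) and 0.72 (arm 2), 12 months' accrual, 18 months' follow-up, two-sided alpha 0.05, power 85%.

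- The plan's figures reproduce. Schoenfeld's formula, events = 4(1.960 + 1.036)² / (ln HR)², gives 283 for HR 0.70 (stated 284) and 333 for HR 0.72 (stated 331).
- With exponential survival, uniform accrual and follow-up f after the last enrolment, the proportion dead is 1 − [exp(−λf) − exp(−λ(f+12))]/(12λ), where λ = HR × ln 2/10. At f = 18 this is 80.5% in control, 68.3% in arm 1 and 69.4% in arm 2. Then 190.5 × (0.805 + 0.683) = 283.6 events in 381 patients, and 221 × (0.805 + 0.694) = 331.2 in 442.
- Trial totals: 331 × 3/2 = 496.5, stated as 497; 0.70 × 497 = 347.9, stated as 348.
- Share of patients reached if every death were reported: 348/738 = 47% at the OS interim and 497/738 = 67% at the final analysis.

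**2. What was tabulated (Table S3).**

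- Fatal SAEs: 26 + 15 + 17 = 58 of 246 + 244 + 246 = 736, or 7.9%. The counts by arm equal those for TEAEs leading to death.
- Any SAE: 135/246 = 54.9% in arm 1 against 101/246 = 41.1% in control, a difference of +13.8 points (Fisher p = 0.003).
- Benmelstobart/anlotinib-related SAEs: 33.7% against 17.5%.

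**3. The literal rule added to the reported rates.** Solving the formula in step 1 for the follow-up at which the three-arm average equals 47% and 67% gives planned death proportions for arm 1 and control of 42.9% and 54.7% at 348 deaths, and 62.8% and 75.4% at 497. The overlap of SAEs and deaths is unknown, so three assumptions are shown. Independent uses 1 − (1 − SAE)(1 − death), nested uses the larger of the two rates, and disjoint uses their sum, capped at 100%.

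| Any SAE, arm 1 minus control | 348 deaths | 497 deaths |
|---|---|---|
| Independent | 74.2 − 73.3 = +0.9 | 83.2 − 85.5 = −2.3 |
| Nested | 54.9 − 54.7 = +0.1 (from unrounded rates) | 62.8 − 75.4 = −12.6 |
| Disjoint | 97.8 − 95.8 = +2.0 | 100 − 100 = 0 |

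**4. What remains once the tables are limited to TEAEs.** Subtracting treatment-related deaths (11, 6, 4) from fatal SAEs (26, 15, 17) leaves 15, 9 and 13 fatal SAEs not classed as treatment-related. How many are progression is not shown. The reported arm 1 minus control difference in fatal events is (26 − 17)/246 = +3.7 points. With progression deaths removed it could lie anywhere between (11 − 17)/246 = −2.4 points (all 15 in arm 1 and none of the 13 in control are progression) and (26 − 4)/246 = +8.9 points (the reverse). These are extremes, and they assume that the treatment-related deaths are all among the fatal SAEs and none is progression.

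**The case against.** The strongest reply is that 10.6 governs reporting to the sponsor and 13.5.2 governs analysis. A progression death in survival follow-up, long after the last dose, is not obviously treatment-emergent and need not reach any table, and the exact TEAE window is properly left to an SAP that is not shown. Section 10.6 also words the fatal case as an explicit exception, and requiring such reports is a legitimate choice. Treatment-related SAEs have their own line, where progression deaths judged unrelated would not appear.

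Most of this stands. A reader might infer that the SAE endpoint mirrors overall survival and hides the toxicity of the active arms. The documents do not support that: fatal SAEs are 7.9%, not near 67%, and the excess is visible in both any SAE and drug-related SAEs. A reader might also infer that the iDMC's safety review is distorted, but section 4.2 does not say how SAEs are presented to it and its guidelines are not shown. Nor do the documents show that AE follow-up in control is cut earlier; that rests on an unquantified guess about when control patients start new treatment, and ending follow-up does not remove a recorded event from its incidence.

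Two things are not answered. Section 13.5.2 does not take out progression deaths that fall within the treatment-emergent window. And the period over which an investigator must report is a matter for the protocol, not the SAP.

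On follow-up of AEs, 3.2.2 is qualified (if possible, or until judged unnecessary), which softens the conflict with 10.4 but does not remove it.

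**Conclusion.** The point holds as a conflict of definitions with an open-ended reporting rule, and as a limited mixing of the efficacy outcome into a secondary safety endpoint. No bias is demonstrated in the reported table.

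Its size in the planned TEAE tables is bounded by the 15, 9 and 13 fatal SAEs not classed as treatment-related, of which an unknown share is progression. The larger effect, in which the 13.8-point excess falls to about 0 to 2 points at 348 deaths and to zero or below at 497, belongs only to a literal count of every follow-up death. It rests on the planned HRs, exponential survival and an assumed overlap of SAEs and deaths, and the reported SAE rates already contain the 58 fatal SAEs. The conflict between 10.4 and 3.2.2 is real but minor.

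**What to change.** - Reconcile section 7 (Post-treatment Follow-ups), section 10.3 (Death and Disease progression), section 10.6, including its last sentence on events leading to death, and section 13.5.2.
- In 10.6, replace the trial-long limb with one stated safety reporting period.
- Keep any expedited reporting of progression deaths that is required, but present SAE incidence and fatal TEAEs with and without progression deaths, and show those deaths on a separate line by arm.
- Reconcile 10.4 with 3.2.2 so that one rule governs follow-up of unresolved treatment-related SAEs and irAEs after new antitumour treatment starts.

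The cost is protocol and CRF-guideline wording and an extra table line. The cause and date of death are already collected in follow-up, and any longer AE follow-up could use the existing 8-weekly contacts.

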## 10.7 Management of SAEs

Any SAE, whether or not related to the study drug, occurring must provide the written report to the sponsor or their representative ([contact]) within 24 hours of being aware of its occurrence, followed by the written follow-up report in detail. For death events, the investigator(s) have to provide the documents (e.g., autopsy and medical report) to the sponsor and ethics committee. The sponsor is required to immediately assess the severity of SAEs, their causality to the study drug, and whether it is an expected event. For suspected unexpected SAEs, the sponsor should quickly report to all participating investigators, clinical trial institutions, and the ethics committee, as well as the Drug Administration; Investigators are also required to inform these suspected unexpected SAEs of the ethics committee.

## 10.8 Management of Common AEs

The dose adjustment of anlotinib due to AEs is listed in section 5.3.2. The type and management of irAEs caused by TQB2450 are listed in the Appendix.

## 11. QoL

The QoL will be evaluated from various aspects through questionnaires. The exploratory objective of this trial is to evaluate the HRQOL, aiming to collect information on drug application as early as possible. The questionnaires for HRQOL will be completed at the scheduled time point.

To avoid being influenced by the investigator(s) or new conditions, the questionnaire should be

completed before any clinical examination and evaluation, as well as any new disease information and new treatment. The questionnaire will be stored as source documents.

Investigator(s) will review the questionnaire and evaluate the clinical signs. Any unobserved AEs in clinical evaluation will be recorded in the CRF.

The EuroQol five-dimensional (EQ-5D) descriptive system consists of a questionnaire and utility value conversion table. The questionnaire is reported for health conditions and EQ visual analog scale (EQ-VAS) score, while the utility value conversion table is reported for EQ-5D index values.

The questionnaire contains EQ-5D health state classifications and EQ-VAS. EQ-5D health state classification contains 5 dimensions, including mobility, self-care, usual activities, pain discomfort, and anxiety/depression. Each dimension contains 3 levels, including no problems, some problems, and extreme problems. EQ-VAS is a 20 cm vertical visual analog scale. 100 at the top indicates the best health you can imagine and 0 at the bottom indicates the worst imaginable health state.

## **12. Data Management**

### **12.1 Data Entry**

The data collected in this trial will be conducted using the electronic data capture (EDC) system. Investigator(s) or designated representative should complete the source document/eCRF timely, accurately, completely, and normatively. Data entry must be performed by authorized personnel who are qualified in EDC operation training.

### **12.2 Data Verification**

Clinical research associates (CRA) have to conduct the source data verification to ensure the accuracy, completeness, consistency, and standardization of the data. Data administrators have to verify the data in the EDC system according to the verification protocol to ensure the accuracy, completeness, and standardization of the data. If any entries into the eCRF are incorrect or incomplete, any discrepancies will be noted in the EDC system by means of electronic data queries. The CRA and data administrators will ask the investigator or CRC to make appropriate corrections. The corrected data will again be reviewed for completeness and consistency.

### **12.3 Data Cleaning**

Data cleaning includes EDC system automatic verification, manual verification, and SAS program cleaning. The investigator or CRC will confirm the questionable data and make appropriate corrections. The corrected data will again be reviewed by CRA and the data administrator for completeness and consistency. If the data queries are addressed, they will be closed, otherwise, they will be noted in the EDC system again until the queries solving.

### **12.4 Electronic Signature**

The investigator is responsible for verifying the authenticity and accuracy of the data reported in the EDC system and making an electronic signature in EDC. The investigator must sign and date the Investigator's Statement of electronic signature before any study-related procedures. It is required to declare that an electronic signature has the same legal effect as a written signature.

## 12.5 Database Locking

The database locking will be confirmed after the completion of data entry, data verification, electronic signature, medical verification, and data verification report. The data administrators will carry out the database locking after completing the listing procedure. The locked database will be not opened in principle.

## 12.6 Data Transfer

After database locking, the data set will be generated by the data administrators and be submitted to the statistician. The eCRF of subjects will be archived in each center.

## 13. Statistical Analysis

### 13.1 Analysis Datasets

**Intention-to-treat (ITT) Analysis Set:** All randomized patients are included for efficacy analysis, according to the ITT principle. For the ITT population, patients will be considered in the treatment group as randomized.

ITT population is the primary analysis set and will be used for all efficacy and baseline characteristics analysis.

**Per-protocol Set (PPS):** All patients of the ITT population who receive the pre-defined minimum cycle of study treatment, had at least one imaging evaluation, without any major protocol deviation, with favorable compliance, and complete CRF.

PPS will be used for the per-protocol analysis of the primary efficacy variable and key secondary efficacy variables. The final PPS will be determined by the principal investigator, statisticians, and sponsors before the database lock.

**Safety Analysis Set (SS):** All randomized patients who receive at least one study treatment and have at least one safety assessment.

SS will be used for the safety analysis. For the SS population, patients will be considered in the treatment group as treated.

Baseline characteristics analysis will be performed for the ITT population. The analysis of the primary efficacy variable will be performed for the ITT and PPS population. The primary set for efficacy is the ITT. The analysis of laboratory data, AEs, and adverse reactions will be performed for the SS population.

### 13.2 Statistical Analysis Plans

#### 13.2.1 General Approach

For quantitative variables, summary statistics will include the number of subjects, mean, standard deviation (SD), median, minimum, and maximum. The decimal places for the minimum or maximum will be the same as that recorded in the database. The decimal places for mean and median will report one more decimal place than the original data values in the database, and standard deviation will report two more decimal places than the original data values.

For categorical variables, frequency counts and percentage of patients will be presented. The percentage will be presented with two decimal places.

### 13.2.2 Size of a Test

#### (1) Type I error control in the multiple-group comparison

There are 3 arms in this trial:

Intervention arm 1: TQB2450, Anlotinib, Carboplatin, and Etoposide

Intervention arm 2: TQB2450 placebo, Anlotinib, Carboplatin, and Etoposide

Control arm: TQB2450 placebo, Anlotinib placebo, Carboplatin, and Etoposide

The primary efficacy endpoints of this trial are PFS and OS. In this trial, a fixed-sequence test will be used for comparisons between treatment groups:

- a) The PFS between intervention arm 1 and the control arm (PFS1) will be first tested with the two-sided significance level of 0.05 (one-side, 0.025). If PFS1 is statistically significant, the OS between intervention arm 1 and the control arm (OS1) will be then tested.
- b) If OS1 is statistically significant, the PFS between intervention arm 2 and the control arm (PFS2) will be tested.
- c) If PFS2 is statistically significant, the OS between intervention arm 1 and intervention arm 2 (OS3) will be then tested.
- d) If OS3 is statistically significant, the OS between intervention arm 2 and the control arm (OS2) will be tested.

The overall significance level is set as 0.05 at two-side (one-side, 0.025). Familywise error rate (FWER) will be controlled by the fixed order test when each hypothesis presupposes the rejection of all previous tests.

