#### 4.1 Sample Size Calculation

##### 4.1.1 Method of Sample Size Calculation

There are 3 arms in this study: Intervention arm 1 (TQB2450, Anlotinib, Carboplatin, and Etoposide); Intervention arm 2 (TQB2450 placebo, Anlotinib, Carboplatin, and Etoposide); Control arm (TQB2450 placebo, Anlotinib placebo, Carboplatin, and Etoposide). The primary efficacy endpoints of this trial are PFS and OS. In this study, a fixed-sequence test will be used for comparisons between treatment groups.

The safety analysis and re-estimation of sample size will be conducted by the Independent Data Monitoring Committee (iDMC). The re-estimation of sample size based on PFS is planned after 50% of the planned PFS events (174 cases). At the same time, a safety analysis will be performed. The interim analysis will be conducted by iDMC. One interim analysis for OS is planned for this study after 70% of the planned OS events. If expected efficacy is observed, early declaration of the study due to efficacy would be considered. The interim analysis will be conducted by iDMC.

The previous study showed that the median OS and PFS in the control arm were 10 and 4 months, respectively [5]. Patients were enrolled within a 12-month accrual period with an 18-month follow-up and were randomly assigned (1:1:1) to three groups. The power was 85% with a type I error rate of 0.050 and a dropout incidence of 10%. The type I error rate in the interim analysis for PFS will be controlled by the Method Based on the Sum of P-values (MSP). The initial sample size in this study will be estimated based on PFS using a computer simulation program.

##### 4.1.2 Sample Size Estimation in the Intervention Arm 1

Assuming that the HR for PFS in the intervention arm 1 compared with the control arm is 0.6, the hazard rate in the intervention arm 1 is 0.1040, and that in the control arm is 0.1733 along with exponential distribution. Approximately 165 PFS events are expected if 174 patients are enrolled. A total of 194 patients are recruited and randomly assigned (1:1) to intervention arm 1 and control arm, considering an approximate dropout incidence of 10%. The interim analysis will be conducted when the planned PFS events are ~83. The final analysis will be performed after ~165 of the planned

PFS events.

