Assuming that the HR for OS in intervention arm 1 compared with the control arm is 0.7, 284 OS events are expected with the type I error rate of 0.050 if 381 patients are enrolled. A total of 424 patients were recruited and randomly assigned (1:1) to intervention arm 1 and control arm, considering an approximate dropout incidence of 10%.

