#### **4.1.3 Sample Size Estimation in the Intervention Arm 2**

Assuming that the HR for PFS in the intervention arm 2 compared with the control arm is 0.65, the hazard rate in the intervention arm 2 is 0.1126, and that in the control arm is 0.1733 along with exponential distribution. Approximately 231 PFS events are expected if 242 patients are enrolled. A total of 270 patients are recruited and randomly assigned (1:1) to intervention arm 2 and control arm, considering an approximate dropout incidence of 10%. The interim analysis will be conducted when the planned PFS events are ~116. The final analysis will be performed after ~231 of the planned PFS events.

Assuming that the HR for OS in intervention arm 2 compared with the control arm is 0.72, 331 OS events are expected with the type I error rate of 0.050 if 442 patients are enrolled. A total of 492 patients were recruited and randomly assigned (1:1) to intervention arm 2 and control arm, considering an approximate dropout incidence of 10%.

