#### **4.1.4 Determination of Total Sample Size**

Considering the sample size estimation in sections 4.1.2 and 4.1.3, 738 subjects will be finally enrolled in this trial and be randomly assigned (1:1:1) to three groups. The interim analysis and final analysis for PFS are conducted for this trial after 174 and 347 cases of the planned PFS events, respectively. The interim analysis and final analysis for OS are performed for this trial following 348 and 497 cases of the planned OS events, respectively.

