### (3) Type I error control for interim efficacy analysis based on OS

One interim analysis for OS is planned for this trial after 70% of the planned OS events (348 cases). If expected efficacy is observed, early declaration of the trial due to efficacy would be considered. The interim analysis will be conducted by iDMC.

Type I error will be controlled by the O'Brien-Fleming spending function approach. According to the O'Brien-Fleming spending function approach, in the interim efficacy analysis based on OS, the one-side significance level is set as  $\alpha_1 = 0.0074$  in the interim analysis and  $\alpha_2 = 0.0228$  in the final analysis.

- In the interim analysis:  $P_1 \leq \alpha_1$ , early declaration of the trial will be considered according to actual results;
- In the final analysis:  $P_2 \leq \alpha_2$ , the between-group difference in OS will be considered statistically significant.

$P_1$  = the one-side P value in the interim analysis;  $P_2$  = the one-side P value in the final analysis;

The tests sequence and type I error in the final analysis are shown in the following figure:

[figure not shown]

A two-sided test with a significance level of  $\alpha=0.05$  will be used for secondary efficacy endpoints and safety analysis. Two-sided  $P \leq 0.05$  will be considered statistically significant with a 95%CI.

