### 13.2.3 Hypothesis

The primary efficacy endpoints of this trial are PFS and OS.

Comparison between groups will be performed using a stratified log-rank test:

➤ PFS hypothesis 1 (Intervention arm 1 vs. Control arm)

$H_{0(PFS1)}$ : PFS in intervention arm 1 = PFS in the control arm, that is,  $S_1(t) = S_2(t)$ ;

$H_{1(PFS1)}$ : PFS in intervention arm 1  $\neq$  PFS in the control arm, that is,  $S_1(t) \neq S_2(t)$ ;

*If the test for PFS does not reject the null hypothesis  $H_{0(PFS1)}$ , all subsequent tests will be terminated; if  $H_{0(PFS2)}$  is rejected, tests will be continued. This result will demonstrate the superiority of PFS in intervention arm 1 compared with the control arm.*

➤ OS hypothesis 1 (Intervention arm 1 vs. Control arm)

$H_{0(OS1)}$ : OS in intervention arm 1 = OS in the control arm, that is,  $S_1(t) = S_2(t)$ ;

$H_{1(OS1)}$ : OS in intervention arm 1  $\neq$  OS in the control arm, that is,  $S_1(t) \neq S_2(t)$ ;

*If the test for OS does not reject the null hypothesis  $H_{0(OS1)}$ , all subsequent tests will be terminated; if  $H_{0(OS1)}$  is rejected, tests will be continued.*

➤ PFS hypothesis 2 (Intervention arm 2 vs. Control arm)

$H_{0(PFS2)}$ : PFS in intervention arm 2 = PFS in the control arm, that is,  $S_1(t) = S_2(t)$ ;

$H_{1(PFS2)}$ : PFS in intervention arm 2  $\neq$  PFS in the control arm, that is,  $S_1(t) \neq S_2(t)$ ;

*If the test for PFS does not reject the null hypothesis  $H_{0(PFS2)}$ , all subsequent tests will be terminated; if  $H_{0(PFS2)}$  is rejected, tests will be continued.*

➤ OS hypothesis 3 (Intervention arm 1 vs. Intervention arm 2)

$H_{0(OS3)}$ : OS in intervention arm 1 = OS in the control arm, that is,  $S_1(t) = S_2(t)$ ;

$H_{1(OS3)}$ : OS in intervention arm 1  $\neq$  OS in the control arm, that is,  $S_1(t) \neq S_2(t)$ ;

*If the test for OS does not reject the null hypothesis  $H_{0(OS3)}$ , all subsequent tests will be terminated; if  $H_{0(OS3)}$  is rejected, tests will be continued.*

➤ OS hypothesis 2 (Intervention arm 2 vs. Control arm)

$H_{0(OS2)}$ : OS in intervention arm 2 = OS in the control arm, that is,  $S_1(t) = S_2(t)$ ;

$H_{1(OS2)}$ : OS in intervention arm 2  $\neq$  OS in the control arm, that is,  $S_1(t) \neq S_2(t)$ ;

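### The 85% power used to size OS2 (arm 2 vs control) is stand-alone power; behind the OS3 gate in 13.2.2, the planned hazard ratios leave about a 2% chance of reaching and winning OS2

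*Protocol*

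**What the plan says.** Section 13.2.2 (1) sets a fixed sequence at an overall one-sided level of 0.025: PFS1 and OS1 (arm 1 vs control), PFS2 (arm 2 vs control), OS3 (arm 1 vs arm 2), then OS2 (arm 2 vs control). Each test requires rejection of all earlier ones. The last step is "If OS3 is statistically significant, the OS between intervention arm 2 and the control arm (OS2) will be tested". The version history shows that version 3.0 put OS3 ahead of OS2.

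Section 4.1.1 gives 85% power as a general planning parameter. For arm 1, section 4.1.2 states: "Assuming that the HR for OS in intervention arm 1 compared with the control arm is 0.7, 284 OS events are expected", with 424 patients for the pair after dropout. For arm 2, section 4.1.3 states: "Assuming that the HR for OS in intervention arm 2 compared with the control arm is 0.72, 331 OS events are expected", with 492 patients for the pair. Section 4.1.4 concludes that "738 subjects will be finally enrolled in this trial", with OS analyses at 348 and 497 deaths. Section 13.2.2 (3) sets one-sided OS levels of 0.0074 at the interim and 0.0228 at the final analysis.

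No HR, event count or power is given for OS3 anywhere. In section 13.2.3, OS hypothesis 3 is headed as arm 1 against arm 2, but its null reads "OS in intervention arm 1 = OS in the control arm, that is", which repeats OS1.

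**The concern.** The two planned OS effects against control are almost equal, so the plan itself implies almost no survival difference between the two intervention arms. Yet a significant difference between those arms is the condition for testing OS2. The sample-size section justifies the trial's size by OS2 and does not mention the condition.

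At stake is a formal overall survival claim for anlotinib plus chemotherapy. Arm 2 could deliver its full planned benefit and the trial would still almost never be allowed to test it. The gate also pulls the wrong way for arm 2: OS3 and OS2 share arm 2 with opposite signs, so a better result in arm 2 makes OS3 harder to win.

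**Working it through.** **1. Reproduce the OS2 sizing (section 4.1.3).**
- Schoenfeld events = 4(z₀.₉₇₅ + z₀.₈₅)² / (ln HR)² = 4(1.960 + 1.036)² / (ln 0.72)² = 333, against 331 stated. With 331 events the power is 84.8%.
- Patients: exponential survival, control median 10 months (hazard λ = ln 2/10), 12 months of accrual and 18 of follow-up (section 4.1.1). P(death) = 1 − (e^(−18h) − e^(−30h))/(12h), where h is the arm's hazard. This gives 0.683 for arm 1 (h = 0.70λ), 0.694 for arm 2 (h = 0.72λ) and 0.805 for control (h = λ). With 221 per arm in the OS2 pair: 221 × (0.694 + 0.805) ≈ 331 deaths.
- Dropout: 442/0.9, rounded up to an even number, = 492.
- The OS1 sizing also reproduces: 283 events against 284 stated.

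So 85% is right as the power of OS2 taken alone.

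**2. Which comparison sets the trial's size.**
- OS2: 492 × 3/2 = 738; 331 × 1.5 = 496.5, i.e. 497; 0.7 × 497 = 348. All match section 4.1.4.
- OS1: 424 × 3/2 = 636.
- PFS pairs: 194 × 3/2 = 291 and 270 × 3/2 = 405.

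Section 4.1.1 says that the initial size rests on PFS, but only OS2 produces 738.

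**3. Power of the gate, OS3.**
- Implied HR = 0.70/0.72 = 0.972, derived under proportional hazards.
- Deaths at 497 in total, split in proportion to the probabilities above: about 156 in arm 1, 158 in arm 2 and 183 in control. OS3 therefore has about 314 deaths.
- Final look alone: Φ(√314/2 × |ln 0.972| − z₀.₉₇₇₂) = Φ(0.25 − 2.00) ≈ 4.0%.
- With 331 deaths it is 4.1% at one-sided 0.0228, or 4.4% at 0.025.
- With both OS looks (0.0074 and 0.0228), simulation gives 4.3%.
- For 85% power, OS3 would need about 45,255 deaths at HR 0.972, or a true HR of about 0.72 with 331 deaths.

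**4. Chance of reaching and winning OS2.** Simulation of 2,000,000 draws of arm-level log hazards with variance 1/deaths, arms shared between comparisons, looks at 348 and 497 deaths, and the PFS gates taken as passed:

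| Event, at planned HRs 0.70 and 0.72 | Probability |
|---|---|
| OS1 | 90.2% |
| OS2 alone | 85.2% |
| OS3 | 4.3% |
| OS1 and OS2 (OS2 placed before OS3) | 79.3% |
| OS1, OS3 and OS2 (order as planned) | 2.1% |

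Once OS1 and OS3 are won, OS2 is won only about half the time (2.1/4.3), because of the negative correlation through arm 2.

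**5. Sensitivity to a larger arm 1 effect** (arm 2 held at 0.72, split of deaths held as above):

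| True arm 1 HR | Implied OS3 HR | OS3 power | OS1, OS3 and OS2 |
|---|---|---|---|
| 0.70 | 0.972 | 4% | 2% |
| 0.60 | 0.833 | 36% | 26% |
| 0.55 | 0.764 | 66% | 52% |
| 0.50 | 0.694 | 89% | 75% |

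**6. The OS3 hypotheses.** Section 13.2.2 (1) c) and the heading in 13.2.3 both say arm 1 against arm 2. The null and alternative lines beneath that heading say arm 1 against control.

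**The case against.** The strongest reply is that the order is valid and deliberate. A fixed sequence controls the familywise error rate whatever the order. Version 3.0 chose this one, and OS3 is the only confirmatory OS test that isolates TQB2450, because arm 2 is the same regimen with TQB2450 placebo. A sponsor may rank that question above an OS claim for arm 2. This stands: the order is not a type I error fault, and changing it is partly a trade-off.

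A second reply is that 0.70 and 0.72 are separate sizing assumptions, not a prediction for arm 1 against arm 2. That also stands as a caveat, since 0.972 is derived. But it is the only OS3 effect consistent with the stated planning values, no other is offered, and the chance of winning OS2 stays below 85% even at an arm 1 HR of 0.50.

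A reader might infer more than the documents support:
- *That the 85% is false.* It is correct as stand-alone power, and the protocol never expressly claims it for OS2 within the sequence.
- *That OS2 has about 4% power in the sequence.* That is the power of the gate; the chance of winning OS2 is about 2%.
- *That the 738 − 636 = 102 patients beyond the OS1 requirement serve OS2 alone.* They also add events to the other tests, and OS1 power rises to about 90%.
- *That arm 2 has no confirmatory route.* PFS2 precedes OS3, and the HR and confidence interval for arm 2 OS can still be reported.
- *That the wrong null in 13.2.3 means the gate is wrongly chosen.* It is a copying error, separate from the power question.

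**Conclusion.** The concern holds as a mismatch between the test order and the sample-size justification. The comparison that sets 738 patients and 497 deaths has 85% power alone but about a 2% chance of being reached and won in the declared sequence. With OS2 ahead of OS3, the chance of winning OS1 and OS2 together is about 79%. The figures assume exponential survival, proportional hazards, the planned HRs, an OS3 HR derived as 0.70/0.72, and PFS1 and PFS2 already won, which favours the plan. Familywise error is unaffected. The loss is confined to the confirmatory OS claim for arm 2.

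**What to change.** - In sections 4.1.3 and 4.1.4, state that 85% for OS2 is stand-alone power and give the power within the sequence (about 2% under the planned HRs, PFS gates taken as passed). State the HR and power assumed for OS3. This costs only wording.
- Keep the 85% statement in section 4.1.1. It also serves PFS1, OS1 and PFS2, so deleting it would remove correct information.
- If OS data are still blinded, consider the order PFS1, OS1, PFS2, OS2, OS3, each at full alpha. It needs no extra patients and leaves familywise error unchanged. The price is that OS3 would be tested only after OS2, which matters if isolating TQB2450 is the sponsor's priority; under the planned HRs, OS3 has only about 4% power wherever it stands. The supplement issued with this protocol already reports response, PFS and safety by arm. If OS has been unblinded too, reordering would be post hoc and only the disclosure remains.
- Separately, rewrite the OS3 null and alternative in section 13.2.3 as arm 1 against arm 2.
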